## Abstract

**Introduction:**

Previous trials of dietary interventions to prevent gestational diabetes mellitus (GDM) have yielded only limited success. Low-carbohydrate diets have shown promise for the treatment of type 2 diabetes, but there is no evidence to support their use in pregnancy. The aim of this study is to explore the feasibility of a moderately reduced-carbohydrate dietary intervention delivered from mid-pregnancy alongside routine antenatal care.

**Methods and analysis:**

This is a feasibility randomised controlled trial (RCT) with embedded qualitative study. Sixty women who are pregnant <20 weeks’ gestation, with body mass index ≥30 kg/m^2^ at their antenatal booking appointment, will be randomised 2:1 intervention or control (usual care) and followed up until delivery. The intervention is a moderately reduced-carbohydrate diet (~130–150 g total carbohydrate/day), designed to be delivered alongside routine antenatal appointments. Primary outcomes are measures of adoption of the diet and retention of participants. Secondary outcomes include incidence of GDM, change in markers of glycaemic control, gestational weight gain, total carbohydrate and energy intake. Process outcomes will examine resources and management issues. Exploratory outcomes include further dietary changes, quality of life, maternal and neonatal outcomes, and qualitative measures.

**Ethics and dissemination:**

This trial was reviewed and approved by the South-Central Oxford B Research Ethics Committee NHS National Research Ethics Committee and the Health Research Authority (Reference: 20/SC/0442). The study results will inform whether to progress to a full-scale RCT to test the clinical effectiveness of the RECORD programme to prevent GDM in women at high risk. The findings will be published in peer-reviewed journals and presented at conferences.

**Trial registration number:**

ISRCTN16235884.

STRENGTHS AND LIMITATIONS OF THIS STUDYThe intervention has been codeveloped by a multidisciplinary team of academic researchers and clinical professionals working in maternity, together with patients, to create a support programme likely to be acceptable to women and suitable for use in routine antenatal care.Quantitative and qualitative analyses will assess the feasibility (adherence and retention rate) and suitability of reducing carbohydrate intake in mid-pregnancy, to inform any progression to a future full trial.Dietary intake will be assessed at only two time points, and we will not be able to assess fluctuations in intake over time.This study is not powered to detect clinical effectiveness of the dietary intervention, and subsequent full-scale trials will be required to assess whether this intervention can effectively attenuate gestational weight gain and improve glycaemic control early in pregnancy, with the prospect of preventing gestational diabetes.

## Introduction

Gestational diabetes mellitus (GDM) is defined as hyperglycaemia that develops or is first diagnosed during pregnancy.^1^ GDM significantly increases the risk for adverse health outcomes for both the mother and the offspring,^2–9^ In the UK, approximately 16% of women who are pregnant develop GDM, but the prevalence reaches up to 25%–30% in women living with obesity.^10^ Excessive gestational weight gain (GWG) has also been proposed as a risk factor for GDM,^11^ and several clinical trials in women with overweight or obesity during pregnancy, have tested whether interventions aimed at limiting GWG could help prevent GDM.^12–24^ Although some trials have been successful in attenuating GWG, the majority have failed to demonstrate a reduced risk of developing GDM.^25 26^

The small number of trials that have shown effectiveness in GDM prevention so far included intensive face-to-face dietetic support and/or provision of key foods to study participants, with no indication of how these strategies could be delivered in routine practice.^14 16 18 22 23^ For example, the Finnish Gestational Diabetes Prevention (RADIEL) study, reduced the incidence of GDM by 39% in women at high risk, but required extra face-to-face visits and a group session to deliver standard healthy eating and physical activity advice, which may not be manageable in routine practice given the amount of appointments women are already required to attend.^14^ The ESTEEM and St Carlos trials implemented a Mediterranean-style diet supplemented with extra virgin olive oil and nuts, provided as part of the trial, from early or mid-pregnancy and showed a similar reduction in GDM risk.^16 23^ Nevertheless, wide scale implementation of a Mediterranean-style diet in the UK could be challenging due to limited understanding of the dietary pattern, differences in dietary habits and preferences, and the cost of extra virgin olive oil.^27–29^

The mechanism behind the success of some dietary interventions over others in preventing GDM remains unclear. Implementation at earlier stages of pregnancy seems to be key, but the optimum dietary composition is unknown. In the RADIEL study, there was only a small improvement reported in adherence to the diet recommendations in the intervention group compared with the control group.^14^ In the Mediterranean dietary interventions, it was speculated that increased unsaturated fat and polyphenol consumption might have been beneficial with regards to insulin sensitivity and inflammation.^16 23^ However, a reduction in dietary carbohydrate as a natural result of higher fat and protein consumption, in conditions when energy intake remains similar, may have also played a role. Indeed, successful interventions to date included some advice for reducing sugar consumption and/or moderating starchy foods.

Low-carbohydrate diets are effective for the management of type 2 diabetes, especially over the short term (3–6 months).^30^ Reducing carbohydrate intake from earlier stages of pregnancy may help reduce hyperglycaemia, independent of effects on weight gain, and may also help attenuate GWG by reducing energy intake. Although low-carbohydrate diets (<130 g/day)^31^ are not recommended for women who are pregnant, due to safety concerns associated with ketosis, research in non-pregnant populations suggests that significant ketosis only occurs when carbohydrate intake is severely restricted to <50 g/day, leaving considerable scope to adopt a reduced-carbohydrate diet.^31^ The level of carbohydrate reduction should be considered carefully though, particularly given that pregnancy is a ketosis-prone state, where ketones may develop at higher carbohydrate intakes than in non-pregnant populations.^32^ One previous randomised controlled trial (RCT) specifically aimed at reducing total carbohydrate consumption as part of an intensive healthy eating intervention.^33^ Despite a substantial significant effect on limiting GWG, the intervention did not reduce GDM incidence. This study was underpowered to detect difference in GDM risk, and it resulted in only a small reduction in carbohydrate intake compared with usual care (reduction of 4.8% of energy intake from carbohydrates, equivalent to about 30 g of carbohydrate per day). Thus, the effect of a reduced-carbohydrate diet as a preventative strategy for GDM remains to be investigated.

We have developed a dietary approach based on moderate carbohydrate reduction suitable for use in pregnancy, combined with behavioural support. The reduced-carbohydrate intervention for the management of obesity and reduction of gestational diabetes (RECORD) also recommends consumption of fresh foods, plenty of vegetables and moderate protein intake. It was designed with midwives and dietitians experienced in working with women who are pregnant, together with patients, and is designed to be delivered alongside routine antenatal appointments. The aim of this trial is to assess the feasibility of the intervention and whether it leads to a substantial reduction in total carbohydrate intake, defined as target mean intake of around 130–150 g/day, that is, reduction of around 80–100 g/day compared with the national average,^34^ for the purposes of this study.

Other objectives include:

To assess the study procedures to inform the design of a full RCT.To assess the potential effect of the reduced-carbohydrate behavioural intervention on markers of glycaemic control, incidence of GDM, GWG, dietary intake, quality of life, and maternal and neonatal outcomes.To qualitatively analyse participant experiences of the intervention.

### Study design

A two-arm parallel group individually RCT, in women who are at <20 weeks’ gestation with a body mass index (BMI) ≥30 kg/m^2^. Participation will last approximately 6 months per participant; from early in the second trimester (no more than 19 weeks plus 6 days), until delivery. Participants will attend two study visits, one at baseline (<20 weeks’ gestation) and one for follow-up, at 24–28 weeks’ gestation.

### Recruitment

Participants will be recruited from one maternity care centre in Oxfordshire, UK. The study is expected to run from May 2021 to December 2022. Women attending the dating or nuchal ultrasound scan appointment (typically between 8 and 14 weeks’ gestation) will be approached to take part in the study. Potentially eligible participants will be provided with the participant information sheet, and invited to give their contact details. A member of the research team will contact the women who were interested in taking part to discuss the study and assess self-reported eligibility to participate according to the full inclusion and exclusion criteria as detailed below. Eligible individuals who wish to participate will be booked in for a face-to-face baseline appointment. The aim is to recruit women as early in pregnancy as possible, therefore, we will aim to book the baseline appointment for the trial within 2 weeks after the dating scan. However, we recognise this extra appointment at short notice may be challenging, and during this feasibility trial we will allow women to attend their baseline appointment up to 20 weeks’ gestation. This allows at least a month to practise the dietary changes and assess whether the progression criteria are met. In addition, we will monitor the timing of the baseline appointment to check whether setting a limit at 14 weeks’ gestation for recruitment to any future definitive trial, would be feasible. For those who decline to participate, permission will be sought to record the barriers to participation.

### Eligibility criteria

#### Inclusion criteria

Pregnant women <20 weeks’ gestation.Aged ≥18 years.BMI ≥30 kg/m^2^ measured at booking appointment.Planned antenatal care and delivery at the study setting.

#### Exclusion criteria

The participant may be excluded if any of the following apply:

Severe congenital fetal anomaly (confirmed by ultrasound).Planned termination of pregnancy or ectopic pregnancy.Prepregnancy diagnosis of diabetes or impaired glucose tolerance or taking metformin.Renal disease.Severe liver disease.Organ transplant.Cardiac failure (grade II New York Heart Association, and more severe).^35^
Severe neurological disorder (including epilepsy).Severe psychiatric disease requiring in-patient admission.GDM diagnosis at the baseline study visit according to the National Institute for Health and Care Excellence (NICE) diagnostic criteria: a fasting plasma glucose level of 5.6 mmol/L or above, or a 2-hour plasma glucose level of 7.8 mmol/L and above.^36^
History or presence of eating disorder.Hyperemesis gravidarum.Unable to understand spoken and written English.Previous bariatric surgery.Women participating in other intervention research studies.Any other significant disease or disorder which may either put the participants at risk because of participation in the trial, or may influence the result of the study, or the participant’s ability to participate in the study.

### Study procedures

The baseline visit will take place before 20 weeks’ gestation, at the hospital, with a member of the research team and lasts for approximately 2 hours. Written informed consent will be sought and eligibility for inclusion will be formally assessed. All participants will complete the following baseline assessments: blood pressure, weight and height measurements, a 2-hour 75 g oral glucose tolerance test (OGTT), a quality of life questionnaire and measurement of their carbohydrate intake as part of a broader assessment of their dietary intake via an online questionnaire. The participants will be randomised to one of the two trial arms. Participants in the intervention group will proceed to receive the intervention session. Due to the nature of the OGTT test and exclusion of women with GDM confirmed on this baseline test, full eligibility can only be confirmed after the visit, therefore after randomisation. While there is controversy over whether true GDM can be diagnosed prior to 24 weeks’ gestation with existing criteria,^37^ the clinical care team advised that women meeting the NICE criteria for GDM at the baseline visit,^36^ should be considered to have GDM and be treated as such. All confirmed eligible participants will be invited to attend a further 2-hour research visit at 24–28 weeks’ gestation where the same research measurements will be collected as a follow-up, and a second OGTT will be completed. Maternal and neonatal outcomes will be extracted from medical records after delivery. The study flow is in figure 1.

**Figure 1 F1:**
[figure not shown]
Study flow. BMI, body mass index; GDM, gestational diabetes; OGTT, oral glucose tolerance test.

### Sample size

This feasibility study is not powered to detect a statistically significant difference in clinical effectiveness between the trial arms. Instead, we will test for reductions in carbohydrate intake as preliminary evidence of the adoption of the reduced carbohydrate diet to an extent that is expected to alter health outcomes. The average total carbohydrate intake in women who are not pregnant is about 230 g/day.^34^ We have set the sample size to be able to detect a reduced target intake at 130–150 g, that is, ~140 g of total carbohydrate/day at follow-up, with 95% CI excluding 170 g/day. Progression criteria to a full trial also include adequate retention of participants as a measure of feasibility. We consider that a minimum of 80% of participants need to complete an OGTT at 24–28 weeks’ gestation, similar to previous trials, with 95% CI excluding 70%.^12 16^ Both progression criteria thresholds are satisfied with a sample size of 60 participants allocated in 2:1 ratio, intervention: control. Unequal randomisation allows us to have sufficient participants in the intervention arm for the qualitative study.

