**Figure 2 F2:**
[figure not shown]
Progression criteria. OGTT, oral glucose tolerance test.

Retention rate: proportion of all participants who complete an OGTT at the follow-up time point, with green light for 95% CI of average completion rate that does not cross 70%. (Evaluated by documentation at 24–28 weeks’ gestation; assessed as the proportion of participants for whom OGTT measurements are available).

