### Retention and withdrawal

This study has been designed to run alongside routine antenatal appointments with remote support elements, to minimise the burden associated with attending extra visits. The brief telephone support sessions with a dietitian will act as prompts for the participants to engage with the intervention and self-monitoring. Participants are asked to attend one visit in addition to routine antenatal care. All of the women who take part would be offered an OGTT at 24–28 weeks of pregnancy for the diagnosis of GDM. The 24–28 weeks follow-up study visit and OGTT, replaces the routine care OGTT and the results are shared with the clinical care team. To compensate for the time and inconvenience in taking part, we offer participants financial incentives for their participation.

Each participant will have the right to withdraw from the study at any time, or may be withdrawn at the discretion of the research or clinical care team. Participants will have the right to withdraw their collected data if they wish. Withdrawn eligible and enrolled participants will not be replaced in this feasibility study. We will only replace participants whose baseline OGTT is abnormal, as they will have consented and been randomised before OGTT results become available, but they will have essentially failed the full screening.

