### Statistical analysis

Descriptive statistics will be used to report the baseline characteristics of each trial arm. Continuous variables will be reported using mean/median and SD/range, while categorical variables will be reported using frequencies and percentages.

Since this is a feasibility study, the primary outcomes are the main progression criteria which will inform the design of a future RCT, powered to detect a significant difference in the efficacy of the intervention in preventing GDM. Descriptive statistics with 95% CIs will be used to analyse and report the progression criteria. For the analysis of the secondary, process-related and exploratory measures, all data collected up to each time point will be used. Descriptive comparative statistics will be used to analyse and report these measures along with 95% CIs (eg, difference in means or proportions between baseline and follow-up for each group or between the two groups). Data from audiorecorded and transcribed qualitative interviews on acceptability and experience of the intervention by participants will be analysed using thematic analysis and reported descriptively.

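### With 60 participants, 80% OGTT completion (48/60) does not give a 95% CI excluding 70%, so the stated retention minimum narrowly misses its own green light

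*Protocol article*

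**What the plan says.** The Sample size section sets the retention requirement in two parts. The first is a level: "We consider that a minimum of 80% of participants need to complete an OGTT at 24–28 weeks’ gestation". The second is a precision condition on that level, "with 95% CI excluding 70" per cent. It then says of retention and carbohydrate intake together: "Both progression criteria thresholds are satisfied with a sample size of 60 participants allocated in 2:1 ratio, intervention: control".

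Under Outcomes, Primary, retention is one of two progression criteria. The measure is the "proportion of all participants who complete an OGTT at the follow-up time point". The decision rule attached to that measure rests on its confidence interval and reads: "with green light for 95% CI of average completion rate that does not cross 70" per cent. The system is a traffic light: green to proceed, amber to proceed with amendments for remediable issues, red not to proceed.

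Two further statements fix the inputs. Under Retention and withdrawal, "Withdrawn eligible and enrolled participants will not be replaced in this feasibility study"; only women with an abnormal baseline OGTT are replaced. Under Statistical analysis, "Descriptive statistics with 95% CIs will be used to analyse and report the progression criteria". The article names no interval method and mentions no one-sided bound.

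**The concern.** The sample size sentence presents 60 as the number at which 80% completion meets the precision condition. If 48/60 does not exclude 70%, the section and the decision rule disagree about the same result: the section presents 80% as meeting the threshold, and the rule does not give it green.

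This is one of two primary outcomes and feeds the decision on a full trial. A team relying on the sentence would take 80% as the working target and find at the end that it falls just short. Near the cut-off the interval also matters: 49/60 is green by Wilson and not green by the exact method.

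**Working it through.** **Inputs.** N = 60, both arms (Sample size; Outcomes, Primary). Minimum completion 80%, so x = 0.80 × 60 = 48. Bound to be excluded: 70%. Confidence level 95%, taken as two-sided, z = 1.96. Withdrawals count against retention because they are not replaced.

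**Reproducing the plan's N.** The simple precision formula with half-width d = 0.10 gives

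N = z² p(1 − p) / d² = 1.96² × 0.80 × 0.20 / 0.10² = 61.5, so 62.

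The stated 60 is within two participants of this and looks like a rounded Wald calculation.

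**Testing the claim at 48/60.**

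Wald: standard error = √(0.80 × 0.20 / 60) = 0.05164; half-width = 1.96 × 0.05164 = 0.1012; lower limit = 0.80 − 0.1012 = 0.6988.

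Wilson: lower limit = [p + z²/(2N) − z√(p(1 − p)/N + z²/(4N²))] / (1 + z²/N) = (0.8320 − 0.1062) / 1.0640 = 0.6822.

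Exact (Clopper-Pearson): lower limit = 0.6767.

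| Interval for 48/60 | Two-sided 95% CI | Excludes 70%? |
|---|---|---|
| Wald | 69.9% to 90.1% | no |
| Jeffreys | 68.6% to 88.6% | no |
| Wilson | 68.2% to 88.2% | no |
| Agresti-Coull | 68.1% to 88.3% | no |
| Clopper-Pearson | 67.7% to 89.2% | no |

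Logit (68.0%), mid-p (68.5%), and the continuity-corrected Wald (69.0%) and Wilson (67.3%) lower limits are also below 70%.

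**Smallest green count with N = 60.**

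| Completers | Wald lower limit | Wilson lower limit | Exact lower limit |
|---|---|---|---|
| 48 (80.0%) | 69.9% | 68.2% | 67.7% |
| 49 (81.7%) | 71.9% | 70.1% | 69.6% |
| 50 (83.3%) | 73.9% | 72.0% | 71.5% |

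Green therefore starts at 49/60 by Wald or Wilson and at 50/60 by the exact method.

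**Chance of reaching each count**, X binomial with N = 60:

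| Rule | True retention 80% | True retention 85% |
|---|---|---|
| at least 48 (plain 80% rule) | 58% | 89% |
| at least 49 (Wald, Wilson) | 45% | 82% |
| at least 50 (exact) | 32% | 72% |

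**The case against.** The best defence is that this is rounding. By Wald the lower limit is 69.88%, a miss of 0.12 points, and the formula asks for 61.5 women against 60. To the nearest per cent the limit is 70%, which arguably does not cross 70%. This stands as a statement about size, and it means that N = 60 needs no change. It does not rescue the sentence: the Sample size section says the interval excludes 70%, and a limit of 70% does not. Wald is also the most favourable of the intervals above; Wilson and exact miss by about 2 points.

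A one-sided 95% bound (a 90% interval) would pass 48/60 by Wald (71.5%) or Wilson (70.3%), though not by the exact method (69.6%). The article says 95% CI and gives no one-sided reading.

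The section can also be read as a joint requirement, at least 80% and a CI excluding 70%, so that a bare 80% was never meant to be green. On that reading the decision rule is intact, but the claim that 60 participants satisfy it at 80% is still wrong. The choice of interval may properly sit in the full protocol or analysis plan, so its absence from the article is not the fault. The fault is that the stated claim fails whichever of these intervals is chosen.

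Three stronger readings are tempting and are not supported:

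- **That 48/60 would stop progression.** There is an amber zone, and the figure holding the progression criteria is not shown. The visible text shows only that 48/60 is not green.
- **That a 45% chance of green at a true 80% shows the study is too small.** Most of that is a cut-off effect. When the true rate sits at the threshold, even a plain rule of at least 48/60 passes only 58% of the time. The defect accounts for the drop from 58% to 45% or 32%. The plan sets a precision target for retention and claims no power for it.
- **That the carbohydrate half of the same sentence is also wrong.** The article gives no SD, so that half can be neither reproduced nor refuted from it.

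**Conclusion.** Wrong as written, of moderate severity. Under every standard two-sided 95% interval examined, 48/60 includes 70%, so the stated minimum misses the stated green rule. The shortfall is 0.12 percentage points by Wald and about 2 points by Wilson (1.8) or exact (2.3). In practice it is one more completer by Wald or Wilson and two more by the exact method.

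This rests on a two-sided 95% interval, a denominator of all 60 participants as the Outcomes section defines it, and independent binomial outcomes for the chances of green. It does not call into question the sample size, the green rule or the definition of retention.

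**What to change.** Keep N = 60 and the CI-based rule.

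1. Name the interval in advance, before retention is assessed, and state the green threshold as the count it implies: at least 49/60 (81.7%) by Wilson, or at least 50/60 (83.3%) by the exact interval.
2. Correct the Sample size sentence so that it no longer says 60 participants satisfy the retention threshold at 80%, and give the chosen count instead.
3. Report the chance of green beside it: at a true 80%, 45% (49 or more) or 32% (50 or more), against 58% for a plain 48/60 rule; at a true 85%, 82% or 72%.

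Declaring 48/60 green is not an equivalent correction, because it would contradict the CI rule in the Outcomes section. No change to the retention denominator is needed.

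The cost is a few lines of wording and a slightly less favourable stated figure (81.7% or 83.3% instead of 80%). No extra participants, visits or data are needed.
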